# Tele-care intervention performed by parents involving specific task- environment- participation (STEP protocol) for infants at risk for developmental delay: protocol of randomized controlled clinical trial

**DOI:** 10.1186/s12887-022-03126-3

**Published:** 2022-01-20

**Keywords:** Intervention, Home intervention, High-risk infants, Tele-care

## Abstract

**Background:**

With the implementation of social distancing due to the Covid-19 pandemic, many at-risk infants are without therapy. An alternative mode of therapy in this situation is tele-care, a therapy in which assessments and interventions are carried out online, in the home environment. We describe a tele-care protocol involving parent delivered task and context specific movement training, participation and environmental adaptation for infants at risk for developmental delay.

**Methods:**

Randomized controlled trial. Infants at risk, with 3 to 9 months corrected age, will be included, and randomized into two groups: control group (conventional guidelines) and experimental group (task, environment and participation in context-specific home program). Infants will be assessed for motor capacity (Infant Motor Profile and Alberta Infant Motor Scale); participation (Young Children’s Participation and Environment Measure) and environment factors (Parent-Child Early Relational Assessment; Affordances in the Home Environment for Motor Development). The intervention period will be 10 weeks, and evaluations will be carried out before and after that period. All the assessment and intervention procedures will be carried out online, with instructions to parents for home therapy. The statistical analysis will be guided according to the distribution of the data, and a significance level of 5% will be adopted. All ethical approvals were obtained by the Ethics Committee of the University of São Carlos (Case number 31256620.5.0000.5504). The protocol will follow the SPIRIT statement. Findings will be disseminated in peer-reviewed publications and presented at national and international conferences.

**Discussion:**

The results of this study will describe the effectiveness of a home intervention, focusing on specific activities, participation and environmental changes. These results will support the implementation of a remote protocol, with lower financial costs and focused on the particularities of the family. This type of care model can possibly help public policies to ensure equal access to evidence-based quality healthcare.

**Trial registration:**

Brazilian Clinical Trials Registry: RBR8xrzjs, registered September 1, 2020.

**Supplementary Information:**

The online version contains supplementary material available at 10.1186/s12887-022-03126-3.

## Background

Functioning refers to the dynamic and positive interaction between the components of body structure and function, activity and participation, under the influence of environmental and personal factors [1]. Currently, an example of the impact of environment factors on the quality of life is the social barrier caused by COVID-19 pandemic. The high number of people infected by COVID-19 has led to an overload of the health care system, even in high-income countries [2–5].

Social isolation has been the main strategy to delay the spread of the virus [6, 7]. Although social distancing has an essential role in the prevention of the COVID-19 spread, studies have shown that social distancing impacts health conditions [8], especially for persons that are physically vulnerable [9]. This occurs because social distancing affects the maintenance of other essential health services [10, 11].

Children at risk for developmental delay might be impacted by social isolation since they usually require the use of health services. Infants at risk for developmental delay are those who have some intrinsic biological risk or risks associated with the mother [12, 13], as prematurity, low birth weight, hypoxemia, use of ventilatory support, cardiorespiratory resuscitation, and prolonged hospitalization [12–14]. These infants usually present delayed motor, cognitive, and behavioral development, besides limitations on functional activities and restricted participation [15].

Due to social isolation, some therapeutic services provided to these children may be limited. Tele-care seems to be an economical way to expand access to infants at risk to health care during social isolation [16]. Tele-care has the advantage of enabling the performance of functional activities by the infants in the home environment, as well as involvement of the family in the rehabilitation process [16]. In addition, tele-care could be inexpensive for patients and institutions, help prevent the spread of the virus, and provide care for these infants.

Some home-based and family-centered interventions have demonstrated positive results in the cognitive and motor development of infants at risk [17–19]. These interventions usually involve the stimulation using functional activities within the child’s home environment, facilitation of caregiver and infant interaction, enrichment of the environment, and optimizes the inclusion of parents in therapy [20]. Studies have shown that family-centered interventions increase the involvement of the parents in setting goals, and the perception of more favorable environments for development [12, 21].

### STEP protocol

This paper describes a tele-care protocol where parents are coached in how to help their child learn. This STEP (specific task- environment- participation) protocol consists of task and context-based activities and enrichment of the environment, using a family-centered approach for infants at high risk for developmental delay. While some protocols of early intervention programs are published [17], we did not find a family-centered intervention protocol that aims to improve functioning (motor capacity, participation) and optimize environmental facilitators (parent-child interaction and physical home environment) in this population. This type of rehabilitation is based on the biopsychosocial approach and, therefore, might improve the health condition and the quality of life of these children [22].

With the application of the STEP protocol, we want to verify which “ingredients” can be successfully applied in a remote intervention and assessment model. This study aims to investigate whether the STEP protocol, offered remotely, can modify the functioning of infants at risk for developmental delay in the first year of life. The main principles of the STEP protocol are shown in Fig. 1.

**Fig. 1 Fig1:**
[figure not shown]
Main principles of the STEP protocol

It is important that the feasibility of online assessment and intervention protocols be studied. More than knowing if telecare works, we must ask ourselves what aspects of this model in question are viable, functional and effective for the population in question, for example dose and type of intervention.

## Objectives and hypotheses

The primary aim of the study is to compare the motor capacity of infants at risk for developmental delay receiving two types of telecare programs. The secondary objectives are to compare the following aspects between the two tele-care programs: a) compare frequency and involvement components of participation at home; b) compare parent-child interaction in aspects of parental behavior, child behavior and dyad of the relationship between; c) compare the availability of toys and affordances in the physical home environment.

We hypothesize that:Infants who receive the the STEP protocol will have higher scores on motor assessments than those who receive the control intervention;Infants who receive the STEP protocol will have higher scores on participation measures compared to the control intervention;Infants who receive the STEP protocol will have higher scores on parent-interaction and home environment measures compared to the control intervention;

## Methods

This study is in accordance with the Declaration of Helsinki. All ethical approvals were obtained by the Ethics Committee of the University of São Carlos (CAAE number 31256620.5.0000.5504). An online consent form will be given to parents, containing an explanation of the study’s assessments, interventions and methodology. The infant will only be included after the caregivers have signed this form.

### Study design

This is a randomized, controlled, parallel, single-blind clinical study. The allocation rate will be 1: 1. The clinical study protocol was based on the Standard Protocol Items: Recommendations for Intervention Trials - SPIRIT guide [23]. This study was registered in the “REBEC” (Brazilian database for the registration of clinical trials) (registration number: RBR-8xrzjs - Available in http://www.ensaiosclinicos.gov.br/rg/RBR-8xrzjs/ - Issue date: 15 Aug 2021; Protocol amendment number: 02) and will follow the standards established by CONSORT [24].

### Study location

The study will be carried out remotely (online) in its entirety. This factor allows infants from any region of Brazil to be invited to participate. Follow-up clinics for at-risk infants will be invited to publicize the research project.

### Sample size

The study will have a non-probabilistic convenience sample. The sample calculation was performed a priori using the G*Power software. Sample size was determined based on the data obtained in the study by Hielkema [25], from the total score of the Infant Motor Profile (IMP) scale. An effect size of 0.23, statistical power of the test of 90% and statistical significance of 5% were considered. The sample calculation resulted in 52 participants. To guarantee a sufficient number of participants, the inclusion of 15% more participants was established in order to meet a possible dropout rate. Thus, the allocation of 30 participants in each group was determined.

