### Statistical analysis

The statistical analysis used will follow the standard principles for randomized controlled studies. The SPSS 17 software will be used for data analysis. The analysis of main interest of the study is the comparison between the groups at the end of the intervention. Data from participants who drop out of the study will be stored and all children entered initially (with assessment of the baseline measures) will be included in the intention-to-treat analysis, with a significance level of *p* < 0.05.

To test the difference between the two groups in maternal and infant characteristics (birth weight, gestational age, sex and corrected age) and in baseline measures (AIMS, IMP, YC--PEM, PCERA and AHEMD-IS) will be used the t test for parametric data and the Mann-Whitney test for non-parametric data. In order to verify the effect of the experimental intervention versus the conventional guidelines for primary and secondary outcomes, the t-test and the Mann-Whitney test will be used. The effect size will be calculated using Cohen’s d.

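### The stated 90% power for an effect size of 0.23 with 52 infants does not hold for the planned end-of-intervention t-test if 0.23 is Cohen's d or the ordinary two-group f

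*Protocol article*

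**What the plan says.** Sample size section: "The sample calculation was performed a priori using the G*Power software", using Infant Motor Profile (IMP) total scores from an earlier study. Then: "An effect size of 0.23, statistical power of the test of 90% and statistical significance of 5% were considered". And: "The sample calculation resulted in 52 participants". A 15% allowance for dropout brings this to 30 per group. The section does not name the effect-size metric, the test family, the number of measurements, the correlation between them, or whether the test is one- or two-sided.

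Statistical analysis section: "The analysis of main interest of the study is the comparison between the groups at the end of the intervention". For the primary and secondary outcomes, "the t-test and the Mann-Whitney test will be used". The effect size is to be reported as Cohen's d. No repeated-measures model is described, although the IMP and the Alberta Infant Motor Scale are taken at T0, T1 and T2 (Outcomes measures section).

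Objectives and hypotheses section: the motor hypothesis is directional; infants on the STEP protocol "will have higher scores on motor assessments than those who receive the control intervention".

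**The concern.** The power statement and the main analysis stand in the same article and do not fit together on either ordinary reading of 0.23. A two-group t-test with 26 per group falls far short of 90% power for a standardised difference of 0.23, or for the 0.46 that a two-group f of 0.23 represents. The only effect-size metric the protocol names is Cohen's d, so a reader will probably take 0.23 to be a d.

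The reading of a null result is at stake. Someone who takes the sentence at face value would treat a non-significant T2 comparison as evidence, at 90% power, against a difference of 0.23. If 0.23 is a d, the test would miss a true difference of that size about 87% of the time (100% − 12.9%). The Discussion links the findings to public health policy, so a wrong reading could matter.

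**Working it through.** **Inputs from the protocol.** Effect size 0.23, power 90%, significance 5%, N = 52 before dropout, 60 after (Sample size); 1:1 allocation (Study design); t-test or Mann-Whitney test at the end of the intervention (Statistical analysis).

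**Assumptions.** Two-sided test, with one-sided also tried because the hypothesis is directional. The correlation between measurements is not given: 0.5 is assumed and 0 to 0.7 tried.

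**1. Reproducing 52.** Take a repeated-measures within-between interaction with 2 groups, m = 2 measurements and f = 0.23. The noncentrality is λ = f²·N·m/(1 − ρ). With ρ = 0.5:

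λ = 0.0529 × 52 × 2 / 0.5 = 11.0, on 1 and 50 df; power = 0.902.

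The smallest even N reaching 90% is 52, which matches. The result depends strongly on the unstated inputs:

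| Measurements | Correlation | N for 90% |
|---|---|---|
| 2 | 0 | 102 |
| 2 | 0.3 | 72 |
| 2 | 0.5 | 52 |
| 2 | 0.7 | 32 |
| 3 | 0.5 | 42 |
| 3 | about 0.38 | 52 |

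The match is therefore not unique.

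**2. The planned t-test.** The noncentrality is d·√(n/2) with 2n − 2 df. For two equal groups, d = 2f, so f = 0.23 gives d = 0.46. At n = 26 the noncentrality is 0.23 × √13 = 0.83 or 0.46 × √13 = 1.66, against a critical value of 2.01.

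| Reading of 0.23 | Power, 26 per group | Power, 30 per group | n per group for 90% |
|---|---|---|---|
| Cohen's d (d = 0.23) | 12.9% | about 14% | 399 |
| Two-group f (d = 0.46) | 37.0% | 41.8% | 101 |

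A one-sided test at 26 per group gives 20.4% and about 50%. The Mann-Whitney test, using its large-sample efficiency of 3/π under normality, gives about 12.5% and 35.5%.

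**3. What 0.23 means in the model that gives 52.** With equal baselines and a between-group difference δ (in SD units) at the second measurement, the four interaction effects are ±δ/4. So f = δ/4 and δ = 4 × 0.23 = 0.92 SD. The planned t-test has 90.2% power for 0.92 SD at 26 per group.

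**4. Detectable difference.** The T2 t-test reaches 90% power at 0.92 SD with 26 per group and 0.85 SD with 30.

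**5. Baseline adjustment.** Adjusting for baseline with correlation r divides the standardised difference by √(1 − r²). At 26 per group and d = 0.23, power is 16% at r = 0.5 and 46% at r = 0.9. For d = 0.46 it is 47% at r = 0.5, 77% at r = 0.8 and 96% at r = 0.9. The difference detectable at 90% power is 0.917 × √(1 − r²): about 0.79 SD at r = 0.5 and 0.65 SD at r = 0.7.

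**The case against.** The strongest reply is that 52 is not a miscalculation. It can be reproduced, and in the model that reproduces it the implied T2 difference is one for which the planned t-test has about 90% power. This stands. A reader might infer from the 13% and 37% that the trial itself has that power. The documents do not support this, because those figures hold only if 0.23 is a d or an ordinary two-group f, and neither reading leads to 52.

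A reader might also go the other way and take it as settled that a repeated-measures interaction was used and that an effect of 0.92 SD was intended. That is an inference too. The correlation of 0.5 is assumed, three measurements with a correlation near 0.38 fit equally well, and the source of 0.23 is not at hand.

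A second reply is that a journal article may leave the metric and test family to a fuller document. As to the bare omission, that is fair. But the article does print a specific power figure and a specific main test, and on either ordinary reading of 0.23 that test does not deliver that power.

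Third, the main test is less settled than it appears, since the Intervention section promises total therapy dose as a covariate, which a plain t-test cannot include. This is true. It adds to the need to state one analysis, but it does not supply the power. Baseline adjustment does not rescue d = 0.23 at any correlation tried, and brings d = 0.46 to 90% only at a very high correlation that the protocol does not claim.

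Finally, a detectable difference of 0.92 SD at 90% power is not the smallest effect that could be found. At 26 per group, power is 80% at 0.79 SD, and an observed difference of about 0.56 SD is already significant. The step from 52 to 60 is not at issue: the text says 15% more, and 52 × 1.15 = 59.8.

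**Conclusion.** The concern holds as a mismatch between the power statement and the planned analysis, not as an arithmetic error in 52. At 26 per group and two-sided 5%, the T2 t-test has about 13% power if 0.23 is Cohen's d and about 37% if it is the two-group f. No one-sided or Mann-Whitney variant comes near 90% on either reading.

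If 0.23 is instead the f of a two-by-two interaction with equal baselines, about 90% power is right, but for a difference of about 0.92 SD that the protocol never states or justifies. Which of these applies cannot be settled from the document. The power calculations are firm; the explanation of where 52 came from is plausible but not established. On any of these readings the sentence needs restating, because it governs what a null result can be taken to show.

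**What to change.** Keep N = 60 and rewrite the Sample size section so that its power statement belongs to the planned analysis:

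- Say which metric and model 0.23 came from, with the number of measurements and the correlation used.
- Replace the claim of 90% power for 0.23 with the standardised T2 difference detectable at 90% power: about 0.92 SD with 26 per group and 0.85 SD with 30 per group (two-sided 5% t-test).
- If the analysis is to be baseline-adjusted instead, say so in the Statistical analysis section and give the detectable difference for a stated assumed correlation. At 26 per group this is about 0.79 SD for a correlation of 0.5 and 0.65 SD for 0.7.

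This changes wording only. No further infants are needed, and the downside is that the stated sensitivity becomes less favourable.

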### Recruitment

The recruitment of participants will take place in two ways: 1) dissemination on social media, radio and e-mail; and 2) contact with professionals at clinics monitoring high-risk infants. In both cases, the initial contact with the parents will be made through an online questionnaire, to verify the initial inclusion criteria. The experimental design, including time points and outcome measures, is represented in the CONSORT flowchart [26] (Fig. 2).

**Fig. 2 Fig2:**
[figure not shown]
CONSORT flowchart for study participants. Legend: CA - corrected age; PCERA - Parent-Child Early Relational Assessment; IMP - Infant Motor Profile; YC-PEM - Young Children’s Participation and Environment Measure; AIMS - Alberta Infant Motor Scale; AHEMD - Affordances in the Home Environment for Motor Development; GAS - Goal Attainment Scale

### Participants

Infants from 3 to 9 months corrected age, of both sexes, and with moderate to high risk for developmental delay will be included in the study. Infants who present at least two of the following biological risks for developmental delay will be included: a) prematurity (< 33 weeks of gestational age); b) low weight; c) asphyxia (Apgar score from 0 to 3 for more than 5 min and / or neurological manifestations in the neonate such as seizures, coma or hypotonia); d) the need for cardiorespiratory resuscitation or the use of oxygen therapy; e) prolonged length of stay in the Intensive Care Unit (more than 7 days); f) Abnormal General Movements, assessed by General Movement Assessment (GMA). Infants with the absent fidgety or abnormal fidgety general movements will be included in the study [27]. The infant will be filmed for 5 min, in the supine position, wearing only a diaper. For infants assessed before completing 3 months of corrected age, writhing movements will be assessed. Infants who have cramped-synchronized movements or poor repertoire will be included [28].

Infants will be excluded from the study if they have: a) primary diseases already diagnosed and congenital diseases; b) suspected or confirmed blindness or deafness; c) unstable health status, such as severe respiratory illnesses and frequent or uncontrolled epilepsy.

The caregivers of the infants will also be participants of the study, since they will apply the home intervention. The caregiver that will be responsible for the intervention at home will be the person that is available to apply the intervention in the specified time and that spends most time with the infant. Thus, participants will also be excluded if they have caregivers/parents with the following characteristics: a) cognitive or motor impairments that prevent the understanding or performance of activities administered at home; b) not fluent in Brazilian Portuguese.

Infants may discontinue their participation in the study in the following situations: a) parental withdrawal; b) not performing intervention procedures in the first 7 days of treatment; c) inability to receive online monitoring and evaluation; d) do not perform at least 75% of the planned therapy sessions at home (controlled at the end of the intervention) or do not perform the interventions for two consecutive weeks (controlled weekly).

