### Randomization

Randomization of participants will take place after parental consent and first assessments. The infants will be randomized into two groups: 1) control group (conventional guidelines) and 2) experimental group (STEP protocol, using an electronic allocation system (www.sealedenvelope.com). The person responsible for generating and controlling the randomization list will be the only person with access to that list, and will not participate in any other part of the study. The list will be stored on the randomization website and can only be consulted by password.

Children will be allocated to the group by randomization in blocks of 6, with a 1: 1 allocation rate. A person responsible for the randomization list will inform the person responsible for the intervention the assigned group, through a sealed envelope containing the group’s information.

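### Adherence rules permit ending an infant's study participation after randomisation, which conflicts with the promised intention-to-treat comparison unless the end-of-intervention assessment is still sought and used

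*Protocol article*

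**What the plan says.** In the protocol article, the Participants section introduces its list with "Infants may discontinue their participation in the study in the following situations". Besides parental withdrawal and inability to receive online monitoring and evaluation, the list contains three adherence rules:

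- early: "not performing intervention procedures in the first 7 days of treatment";
- during the programme: "do not perform the interventions for two consecutive weeks (controlled weekly";
- at the end: "do not perform at least 75% of the planned therapy sessions at home (controlled at the end of the intervention".

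The Randomization section fixes the order of events: "Randomization of participants will take place after parental consent and first assessments". All three adherence rules therefore operate on infants who have already been allocated.

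The Statistical analysis section states: "The analysis of main interest of the study is the comparison between the groups at the end of the intervention". Of children who leave, it says "Data from participants who drop out of the study will be stored", and it adds that "all children entered initially (with assessment of the baseline measures) will be included in the intention-to-treat analysis". The between-group tests named are the t-test and the Mann-Whitney test. Under Outcomes measures, IMP and AIMS are taken at baseline (T0), after 5 weeks (T1) and after completion of the intervention (T2). The other outcomes are taken at T0 and T2.

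**The concern.** The list ends participation in the study, not only in the home programme. The 75% rule shows the problem most clearly. It is judged when the intervention is over, so there is no treatment left to stop, and the only things it can still affect are whether T2 is collected and whether it is used. Either effect conflicts with the promise to analyse every child who has a baseline.

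Adherence is observed after allocation and may depend on it. STEP activities are individualised and tied to goals the parents choose, whereas control guidance is general. Under Delivery and fidelity, the diaries are reviewed by the treating therapist, who according to the Blinding section cannot be blinded. Low adherence may also go with family circumstances or with the infant's progress. A comparison restricted to adherent families could then differ between arms for reasons other than the intervention, while still carrying the intention-to-treat label. A later analysis plan could not recover T2 values that were never collected.

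**Working it through.** **1. What the 75% rule means in sessions.** The Intervention section sets 5 days a week, and the abstract's Methods give 10 weeks. Taking one session per planned day (an assumption), there are 5 × 10 = 50 planned sessions, and 0.75 × 50 = 37.5. A family with 37 sessions falls under the rule and a family with 38 does not. This is decided at about the time T2 is due.

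**2. The sections side by side.**

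| Section | What it fixes | Consequence |
|---|---|---|
| Randomization | Allocation after consent and baseline | Every adherence rule acts after allocation |
| Participants | Low adherence may end study participation | T2, and for early cases T1, may not be obtained |
| Statistical analysis | All children with a baseline are in the analysis; main comparison at end of intervention | Each child needs an observed or imputed T2 value |

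The first and third rows are compatible with the second only if discontinued infants are still assessed at T2 and those values are used. The article does not say that they are.

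**3. Size of the bias if T2 is lost or set aside.** The documents give no removal rates and no relation between adherence and outcome, so both are assumed. Take no true effect, and let adherence and outcome be standard normal with correlation r in each arm. Remove the least adherent share p of an arm. The mean outcome of those retained is

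r × φ(z) / (1 − p), where φ is the standard normal density and z cuts off a proportion p.

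- p = 0.10: 0.1755 / 0.90 = 0.195, times r.
- p = 0.30: 0.3477 / 0.70 = 0.497, times r.
- Difference: 0.302 × r, which is 0.060 SD at r = 0.2, 0.091 at r = 0.3 and 0.151 at r = 0.5.

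With 30 per group, 27 and 21 infants remain. The two-sided type I error is then about 5.5% (r = 0.2) to 8.1% (r = 0.5) instead of 5%.

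Other assumed pairs give:

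| Removed, one arm v other | Spurious difference, r = 0.2 to 0.5 |
|---|---|
| 10% v 10% | 0 |
| 5% v 15% | 0.03 to 0.08 SD |
| 10% v 20% | 0.03 to 0.08 SD |
| 10% v 30% | 0.06 to 0.15 SD |
| 15% v 35% | 0.06 to 0.15 SD |

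The arm that loses more families looks better. Exchanging the arms reverses the sign, so the bias may favour either one. The zero in the first row also requires r to be the same in both arms.

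**4. The planned effect size, to see whether it can serve as a yardstick.** The Sample size section gives an effect size of 0.23, 90% power, 5% significance and 52 participants. The figure of 52 reproduces for a two-group, two-time-point repeated-measures interaction with Cohen's f = 0.23 and an assumed correlation of 0.5. The noncentrality is 0.23² × 52 × 2 / 0.5 = 11.0, and the power is 0.902. Read as a standardised mean difference, 0.23 would need 398 per arm. On the reading that reproduces 52, the SD of a change equals the outcome SD, and the implied between-arm difference in change is √(11.0 / (52/4)) = √(11.0/13) = 0.92 SD. The value 0.23 is therefore not in the units of the biases in step 3.

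**The case against.** The strongest reply is that loss of T2 is inferred. The Participants section uses permissive wording, nothing there says that T2 is withheld, and the order of the 75% check and the T2 assessment is not stated. The Statistical analysis section excludes nobody and says that data from drop-outs are kept. Missing T2 values could be imputed, and the method for that may properly sit in a fuller protocol or analysis plan that is not shown. The participant flowchart is not shown either. All of this stands, and it is why the point is conditional. It does not remove the conflict, because storing earlier data is not the same as collecting T2, and a rule that may end study participation can create missing outcomes that need not arise.

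Three stronger readings are tempting, and the documents do not support them.

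- *That the intention-to-treat analysis is already defeated, or that infants are removed as a matter of course.* The wording permits discontinuation and does not require it.
- *That STEP will lose more families because it asks more of them.* Table 1 gives both arms the same motor schedule, and the participation and interaction components have no measured dose, so they are unlikely to count towards the 75%. Parent-chosen goals could equally raise adherence.
- *That the bias approaches the planned effect of 0.23, or that removals will exceed the 15% dropout allowance.* The first compares unlike units: on the reading that reproduces 52, the planned effect is about 0.92 SD in change, so 0.15 SD is about a sixth of it (0.15 / 0.92 = 0.16). The second has no basis, because no removal rate is given and nothing says that the 15% leaves out adherence discontinuations.

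**Conclusion.** The point holds as a conflict between two stated provisions. The Participants section permits ending study participation for low adherence after randomisation. The Statistical analysis section promises an analysis of every child with a baseline at the end of the intervention. If the first is applied so that T2 is not collected or not used, the result is a comparison of adherers under an intention-to-treat label.

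The size cannot be derived from the documents. Under the 10% v 30% removal scenario with a correlation of 0.2 to 0.5, all assumed, it is about 0.06 to 0.15 SD in either direction. It is smaller for smaller differences in removal, and zero if removal is equal and related to outcome in the same way in both arms. It is also zero if all randomised infants are followed to T2 and analysed as randomised. The potential bias is modest, but it falls on the primary comparison and is cheap to avoid.

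**What to change.** Reconcile the Participants and Statistical analysis sections in one amended paragraph:

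- Separate stopping the home programme from leaving follow-up. When the programme should stop is for the investigators and is not addressed here.
- State that T1 and T2 are sought from every randomised infant unless consent is withdrawn, whatever the adherence.
- State that all infants are analysed in the group to which they were randomised.
- Use the 75% threshold only to define a supplementary per-protocol set.

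A likelihood-based mixed model that uses the T1 values of IMP and AIMS for infants who still lack T2 is an option, but the conflict can be resolved without it.

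The cost is the amended text and a few additional T2 assessments. These are already done online and concern families already enrolled.
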